## 1. SUMMARY

The need for specifically adapted measures to assess the strength and residual function of upper limbs in non-ambulatory patients with neuromuscular diseases (particularly Duchenne muscular dystrophy and Spinal muscular atrophy) is still relevant.

Both for a regular monitoring of the clinical evaluation in non-ambulatory patients with neuromuscular diseases and for supplying with a system of quantitative measures for research, the **Pré-Acti** project proposes a continuous and homeevaluation of a complete measuring system of muscular activity in non-ambulant patients.

The principle of the measures consists in the use of the accelerometry and magneto-inertial sensors, an innovative technology invented and developed by the SYSNAV Company., for the evaluation of the linear and angular velocity

The system aims to measure the physical activity of a patient as measured by the sensors in the three dimensional space; data are recorded by the sensors attached to one of his upper limbs.

Ten non-ambulatory patients will be included and assessed at the inclusion and fourteen days later. Patients will wear a small plastic watch-like device during the evaluations and at home for fourteen days.

According to this protocol, we want to demonstrate that the simultaneous recording of linear accelerations and angular velocities in the three axes in non-ambulatory patients with myopathies can be assessed at home in a simple, reliable and reproducible manner and can evaluate the activity of upper limbs. Therefore, the purpose of **ActiMyo** is to provide a primary outcome measure that could be used in clinical trials and clinical follow-up for patients.

## 2. INTRODUCTION

Duchene muscular dystrophy (DMD) is the most common muscular dystrophy in children. It is a X-linked genetic disease with an incidence of 1/3500 male births (Emery 1991) with a progressive evolution, leading to the loss of walking in the second decade and death in the fourth decade (Kohler et al. 2009). It affects all the muscles of the body with a progressive restriction of the use of upper limbs. The treatment by glucocorticoids is nowadays the only one considered to have an effect by slowing down the regression of loss of muscle strength and power (Manzur et al., 2008).

The absence of dystrophin in DMD is due to different mutations in the dystrophin gene, disrupting the reading frame. Given the organization in 79 exons of the gene, the reading frame can be restored by the exclusion of one or more exons if the local phase is right. This therapy is called exon skipping (Aartsma-Rus et al., 2002). These days several trials by exon skipping therapy are already underway or will start soon (Nelson et al., 2009). A very important aspect is the need to base the clinical trials on reliable and validated measures, that is to say, reproducible, sensitive, and objective.

After the treat-NMD workshop of 11 July 2007, the need for specifically adapted measures to assess the residual strength of upper limbs in non-ambulatory patients was raised (Mercuri et al, 2008). Therefore, different scales have been proposed, including the Hammersmith Motor

---

 Emery, A. E. (1991). "Population frequencies of inherited neuromuscular diseases--a world survey." Neuromuscul Disord **1**(1): 19-29.

 Kohler, M., C. F. Clarenbach, et al. (2009). "Disability and survival in Duchenne muscular dystrophy." J Neurol Neurosurg Psychiatry **80**(3): 320-325.

 Annemieke Aartsma-Rus, Mattie Bremmer-Bout, Anneke A. M. Janson, Johan T. den Dunnen, Gert-Jan B. van Ommen, Judith C. T. van Deutekom, Targeted exon skipping as a potential gene correction therapy for Duchenne muscular dystrophy, *Neuromuscular Disorders*, Volume 12, Supplement 1, October 2002, Pages S71-S77, ISSN 0960-8966, DOI: 10.1016/S0960-8966(02)00086-X.

The objective of this study is to develop a tool capable to demonstrate the clinical impact of an intervention in patient's daily life, the essential component of medicine and rehabilitation (Bonato, 2005), and at the same time, to improve the monitoring of the disease progression.

#### **4. OBJECTIVES**

Pré-Acti is a study of validation. It consists of highlighting the relevance of a clinical measure at home using ActiMyo for non-ambulant patients with neuromuscular diseases.

This protocol aims to demonstrate the following:

- 1) the feasibility
- 2) the reliability
- 3) the validation of the recorded data by ActiMyo.

Therefore, the objective of this study is to envisage a new clinical measure adapted for non-ambulatory patients with neuromuscular diseases.

#### **5. METHODOLOGY**

We plan to include 10 non-ambulatory patients with neuromuscular diseases (DMD, SMA) older than 10 years old. The non-ambulatory patients followed at the Institute of Myology and in the Pediatric Neurology department of the CHU of Amiens will be requested to participate in this study. They will be selected by Doctor [name] at the Institute of Myology and by Doctor [name] at the Hospital of Amiens.

Muscle evaluations will be conducted in the laboratory of Neuromuscular Physiology, headed by [name] at the Institute of Myology. All the tests will be conducted for neuromuscular patients during a scheduled visit to the Institute of Myology. Patients who want to participate in the study will receive a copy of the information form. The reading of it will be organized during a meeting with an investigator. Once this reading is done and the consent is signed, patients can be included in the study.

#### **6. THE INCLUSION CRITERIA**

The patients have to satisfy the following criteria:

- older than ten years old
- confirmed diagnosis of a neuromuscular disease (DMD, SMA) by the genetics or by the muscular biopsy
- not able to walk ten meters without outside human help or cane
- able to sit on a wheelchair during at least three hours
- assigned to a social security system
- signed informed consent

## **7. THE EXCLUSION CRITERIA**

- Severe cognitive disorders which limit the understanding of the performed tasks
- Acute neurological, inflammatory, infectious, endocrine or orthopaedic pathologies in the last month before the inclusion.
- Scheduled surgery in three weeks after the inclusion
- Upper-limb surgery three months before the inclusion
- Pregnant or breast-feeding women

## 8. WORKFLOW TABLE

**Table 1. Events Calendar**

|                                                              |                                    | D0         | D0–
D14 | D14        |
|--------------------------------------------------------------|------------------------------------|------------|------------|------------|
| Environment                                                  |                                    | controlled | free       | controlled |
| Collection of medical data                            |                                    | x   |            |            |
| Intercurrent events                                   |                                    |            |            | x   |
| Strength tests                                        | Hand Grip test              | x   |            | x   |
|                                                              | Pinch Test                  | x   |            | x   |
| Standardized tasks (scores)

+ ActiMyo          | Box and block test          | x   |            | x   |
|                                                              | Minnesota test (variant)           | x   |            | x   |
|                                                              | Moviplat                           | x   |            | x   |
| Tests of a daily life (scores) +
ActiMyo          | Typing a phrase on the
computer | x   |            | x   |
| Free movements

+ ActiMyo                       | Buttoning up a jacket              | x   |            | x   |
|                                                              | Having lunch                       | x   |            | x   |
|                                                              | Brushing the teeth                 | x   |            | x   |
|                                                              | Writing a phrase                   | x   |            | x   |
| ActiMyo continuously
(approximately 15h/d)

+ Diary |                                    |            | x   |            |

## 8.1. GENERAL COURSE OF THE STUDY

During their first visit, the patients will meet a medical investigator who will give them an information form for reading and will answer their questions. The informed consent will then be collected and medical data will be written down (weight, size, pathology, Brooke and Walton score, and medical-surgical history). The patients will receive all the necessary information regarding the use of the **Actimyo** device (see below). The patients will be then asked to perform series of tasks in upper limbs, the accelerations and angular velocities will be recorded by the **Actimyo** device. All the tests take about three hours. This first phase is intended to correlate the measurements with the results validated in controlled environment.

Thereafter, the patients will be trained to wear the Actimyo device for two next weeks. The recordings will be only during the day, the batteries of the device must be recharged every night. The patient will be asked to remove the device when having a bath in order to avoid immersion. In all, about fifteen hours of usual activity will be recorded daily in subject's environment. Throughout this period, the patient will maintain a diary of his daily activities, making notes by themselves or by a close relative, the time of the beginning and the end of the activity (for example brushing teeth, eating, using the computer, and dressing). [Appendix 1]

In two weeks, the patients will return to the centre with the **Actimyo** device and the same series of tests will be recorded.

## 8.2. PROGRESS OF THE EVALUATION

In the controlled environment, there are the following tests:

- Tests of strength
  - *Hand Grip* – dominant then non-dominant hand, three trials
  - *Pinch* test - dominant then non-dominant hand, three trials
- Quantified tests (with scores)

- *Box and block* test - dominant then non-dominant hand, three trials
- Minnesota test (variant) - dominant then non-dominant hand, three trials
- Moviplat - dominant then non-dominant hand, three trials
- Continuous typing a phrase on the computer: "*Les pompiers sont partis de la caserne avec leur camion rouge*" ("The fire brigade left the fire station with their red truck") - dominant hand, three tries
- Buttoning up a jacket – (device on the dominant hand), one try
- Free movements
  - Having lunch (device on the dominant hand)
  - Brush the teeth (device on the dominant hand)
  - Writing the phrase (device on the dominant hand) "*Les pompiers sont partis de la caserne avec leur camion rouge*" ("The fire brigade left the fire station with their red truck ")

## 9. DESCRIPTION OF THE EVALUATION

**Actimyo** (Bere et al. 2011) is a system which aims to measure the physical activity of a patient from the extraction of the data recorded by sensors fixed on the limb and on the electric wheelchair.

It consists of one or more sensor blocks, a sensor/PC interface (wheelchair box) and the software of data acquisition/decoding installed on the PC. Each block consists of an accelerometer, a gyroscope, and a magnetometer, measuring respectively the acceleration and the angular speed in the magnetic field in three spatial axes. It is fixed on the limb for which we plan to study the movement. The sensor/PC interface synchronizes with sensor blocks and can centralize the data. The software can decode the data and recover them as Excel files. All

---

 Elodie Béré, Mark Benoit, David Vissière, Jacques Duchêne, [name], Laurent Servais, *Actimetry & Neuromuscular Disorders: a system suitable for upper limb evaluation*, Myology 2011

connections Sensors ↔ Interface ↔ PC are through Bluetooth radio transmission. The sensors and the interface box are autonomous from the point of view of energy. The functioning will be based on rechargeable batteries at night.

The sensor block will be protected by a plastic box as shown and worn as a watch on the wrist of the dominant limb on Monday, Wednesday, Friday and Sunday, and on the non-dominant limb on Tuesday, Thursday and Saturday. Another sensor block may be placed on the wrist of the non-dominant limb. The plastic box is small and light enough (38 g, 43/33/20 mm) not to intervene with the subject's movement. [Appendix 2]

**Handgrip** is a tool to measure the strength of the palmar grip of the subject. The patient will grasp as hard as possible the handle of Handgrip, first with his dominant and then with his non-dominant limb. Three consecutive trials will be done on each side. [Appendix 3]

**Pinch test** is a tool to measure the strength of the thumb-index pinch. The patient will pinch the measurement tool as strongly as possible with his dominant and non-dominant limb. Three consecutive tries will be realized on each side. [Appendix 4]

**Box and Block Test (BBT)** is a manual dexterity test, originally developed for adults with cerebral palsy (Mathiowetz et al., 1985). The test consists of a box separated on two equal compartments; one of them contains a number of wooden blocks. The patient will be asked to grab each block with one hand and put it into the empty compartment. The score corresponds the number of blocks moved to the other side during sixty seconds. The test is performed three times, alternating dominant and non-dominant limb. [Appendix 5]

**Minnesota manual dexterity test** is a standardized test, which can assess the ability of the subject to move discs for small distances. It is commonly used for the evaluation of professional competence, for the disability assessment (Gloss et al., 1982), and rehabilitation. We propose seven various wooden discs, coloured on one side, arranged in inverted "V". The patients have to turn the discs on the coloured side, starting with his dominant side, then on the uncoloured side for sixty seconds. The score corresponds the number of returned discs. Three tries will be realized alternately on each side starting with the dominant hand. [Appendix 6]

**Moviplat** is a device developed by the Institute of Myology and has been validated for DMD patients (Servais et al., 2010). The device includes two platforms. The aim is simply to touch alternately each platform. These platforms are connected to the force sensor, which directly measures the developed strength. A counter indicates the number of contacts and a chronometer

counts the time on a selected duration. The score corresponds the number of pair contacts for thirty seconds. Three tries will be realized alternately on each side starting with the dominant hand. [Appendix 7].

**Typing a sentence on the computer keyboard** is a task of daily life. We ask a subject to type with one finger of the dominant hand as many times as possible for sixty seconds the following sentence (no punctuation, no capital letters, and no corrections): "*Les pompiers sont partis de la caserne avec leur camion rouge*" ("The fire brigade left the fire station with their red truck."). The score corresponds the number of characters (including spaces) typed. The test will be done tree times.

**The buttons of the jacket:** The patient will be asked to button up a jacket, the sleeves of which have been previously strung, for sixty seconds. The score corresponds the number of buttoned buttons.

**Free movements:** According to this protocol, the patient will receive a meal of his choice (a meal ticket in the cafeteria). The recording will be made during the consumption of it. During the second recording, fifteen days later, the patient will be asked to choose the same meal. The patient will also be asked to brush the teeth (toothpaste lying on the toothbrush and toothbrush placed on the edge of the sink and brush for sixty seconds). The patient will also be recorded for a minute by ActiMyo during manual writing of the sentence "*Les pompiers sont partis de la caserne avec leur camion rouge*" («The fire brigade left the fire station with their red truck.»). All these tasks will be fulfilled once, without specific instruction, (patients with muscular dystrophy have many adaptation strategies).

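### Buttoning is scored as a count over a fixed sixty seconds with no completion time, so anyone who finishes the jacket early gets the same maximum score; the buttoning and writing recordings may also include rest (minor)

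*Protocol*

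**What the plan says.** **Buttoning.** Section 9: "The patient will be asked to button up a jacket, the sleeves of which have been previously strung, for sixty seconds". Then: "The score corresponds the number of buttoned buttons". Section 8.2 lists the task with the quantified, scored tests, with the device on the dominant hand and one try. Table 1, as extracted, groups it with the free movements, but section 9 defines a score either way.

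**Handwriting.** Section 9: "The patient will also be recorded for a minute by ActiMyo during manual writing of the sentence", the sentence being "Les pompiers sont partis de la caserne avec leur camion rouge". Of the free movements as a group, section 9 adds: "All these tasks will be fulfilled once, without specific instruction". Section 8.2 lists "Writing the phrase (device on the dominant hand" under free movements, and no score is defined for it.

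**Contrast.** For the same sentence on a keyboard, the patient is to "type with one finger of the dominant hand as many times as possible for sixty seconds the following sentence". That task cannot run out before the minute does. Nor can the Moviplat contacts or the Minnesota discs, which are turned one way and then back.

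**Use.** Section 18.2 relates the scores to the accelerations, or to another activity summary that it leaves open, by linear correlation. It estimates reliability by ICC and uses the controlled recordings to recognise tasks at home. Neither buttoning nor handwriting has a completion time or a rule for ending the recording when the task is done.

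**The concern.** A count over a fixed window measures speed only while there is work left to count. On one jacket the work can run out. Patients who finish at 20 s and at 50 s then receive the same score, although one is more than twice as fast. Section 6 restricts walking ability but sets no upper limit on hand function, so such patients are eligible.

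Buttoning is done once per visit in a study of 10 patients, so each capped patient is a tenth of the data for that item. If the examiner does not note when the last button was closed, no later analysis can restore the lost ranking. For the recordings, a hand at rest after completion lowers any summary taken over the whole minute and adds rest to the segment used as a pattern for home task recognition.

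**Working it through.** The protocol gives no figure to reproduce here. Button count, seconds per button and writing speed are not in the documents; the values below are assumptions shown as ranges.

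**Buttoning.** Let B be the number of buttons and t the seconds per button.

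- Score = min(B, whole part of 60/t). Idle time = max(0, 60 − B·t).
- The jacket is finished early when t < 60/B: 60/4 = 15 s, 60/5 = 12 s, 60/6 = 10 s, 60/8 = 7.5 s.

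| t (s) | Possible in 60 s | Score, B = 5 | Idle, B = 5 | Score, B = 8 | Idle, B = 8 |
|---|---|---|---|---|---|
| 4 | 15 | 5 | 40 s | 8 | 28 s |
| 6 | 10 | 5 | 30 s | 8 | 12 s |
| 8 | 7 | 5 | 20 s | 7 | 0 s |
| 10 | 6 | 5 | 10 s | 6 | 0 s |
| 15 | 4 | 4 | 0 s | 4 | 0 s |
| 20 | 3 | 3 | 0 s | 3 | 0 s |

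With 5 buttons, patients from 4 to 10 s per button all score 5. Scored per minute of task time they separate: 5 × 60/20 = 15, 5 × 60/30 = 10, 5 × 60/40 = 7.5 and 5 × 60/50 = 6. Patients who do not finish have a task time of 60 s, so their score is unchanged.

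**Handwriting.** The sentence has 61 characters including spaces (11 words). At v characters per minute, writing takes 60 × 61/v seconds. If it is written once and the recording runs the full minute:

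- 61 per minute or slower: no idle time;
- 80: 45.8 s writing, 14.2 s idle (24%);
- 100: 36.6 s writing, 23.4 s idle (39%);
- 120: 30.5 s writing, 29.5 s idle (49%).

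**Illustration for the correlation.** Simulated samples of 10 had log-normal rates (log-SD 0.5), movement intensity proportional to rate with log-noise 0.3, and a signal averaged over all sixty seconds. Without cap or idle time the mean correlation of rate with signal is 0.83. The correlation of capped score with signal is:

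- 5 buttons: 0.82, 0.70 and 0.47 when 3%, 33% and 64% finish early;
- 8 buttons: 0.83, 0.80 and 0.72 when about 0%, 8% and 28% finish early.

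**Illustration for the ICC.** Two visits, a 5-button cap, between-patient log-SD 0.5, and within-patient log-noise 0.15 or 0.30. With about a third of scores capped, the ICC moves from 0.89 to 0.87 and from 0.69 to 0.67. With about 70% capped, it moves from 0.90 to 0.84 and from 0.70 to 0.62.

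Both simulations show direction under stated assumptions. They do not predict what this study will find.

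**The case against.** **The cap may never bind.** These are non-ambulatory patients with DMD or SMA, and section 13 foresees that some will not manage a task at all. The protocol thus expects trouble at the floor, not the ceiling. This stands as a limit on size: the documents cannot show that anyone finishes early.

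**Handwriting has no score.** This stands. A reader might infer a capped handwriting score from the fixed minute, but section 9 defines none, so no handwriting score enters the correlation. Doing the task once may also mean one attempt: the same sentence covers toothbrushing, which lasts sixty seconds. Rest after writing is therefore possible, not certain.

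**Idle time can be trimmed later.** The signal is stored and section 18.2 leaves the activity summary open; the analysis window may properly be set in an SAP. This largely answers the point for the recordings. It does not answer it for the buttoning score, which is a count taken by the examiner. Reading the finishing time back from ActiMyo would let the device under validation supply its own comparator.

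**Two stronger readings are not supported.** One is that capped scores agree between visits because of the cap and so flatter reliability. A ceiling also shrinks between-patient variance, and in the illustration the ICC falls. The other is a large expected loss of correlation for handwriting. Speeds uniform over 30 to 120 characters per minute, intensity proportional to speed and 10% noise give 0.67 over the fixed minute against 0.96 over writing time. That rests on a speed range with no source in the protocol, a writing speed it does not collect, and a whole-minute mean it does not prescribe.

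**Conclusion.** The concern holds in a narrow form and is minor. The stated buttoning rule gives every early finisher the same maximum score, and no completion time is kept from which to separate them. The buttoning recording then includes rest, and the writing recording may do so.

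The size is conditional: nil if nobody finishes early, with the threshold at 12 s per button for an assumed 5 buttons and 7.5 s for 8. Where the cap binds, differences among the ablest patients are lost from both the score-acceleration correlation and the ICC. Dilution of the recordings further requires a summary over the whole minute, which the protocol does not fix. The buttoning score is the part to settle before the visits, because it alone cannot be repaired afterwards.

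**What to change.** In section 9:

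1. Stop the buttoning clock when the last button is closed or at sixty seconds, whichever comes first. Record that time, and score buttons per minute of task time.
2. Note the time at which the sentence is finished.
3. Compute the ActiMyo summaries for both tasks over task time only.

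The cost is one time field per task on the results form already provided for in section 10, and recorded segments whose length varies between patients. No extra visit, device or patient is needed.

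Repeating the sentence for the whole minute, as in the typing task, is not recommended: it would turn a free movement, meant to be done without specific instruction, into a second speed test of a sentence already tested at the keyboard.
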